### Additional Risks of High Sodium Intake During Childhood

Beyond the concerns of high sodium diets raising blood pressure, there is evidence in children to indicate that higher intake of sodium is associated with increased risk of overweight and obesity. There are now data from three large population-based nutrition surveys in children and adolescents (ie, Great Britain [47], Australia [48], and the United States [49]) that support the link between dietary sodium intake and obesity via greater consumption of sugar-sweetened beverages (SSBs). Remarkably similar results have been observed across each country whereby sodium intake was positively associated with SSB consumption, which in turn is an important risk factor for obesity [50]. However, more recent evidence suggests that sodium intake is associated with adiposity, independent of energy intake [51]. To date, no study has utilized a reliable marker of sodium intake (24-hour urinary sodium excretion) to examine the association between sodium intake and measures of adiposity in Australian children. As overweight and obesity follows a trajectory over the life course [52], it is important to understand the association between these risk factors and 24-hour urinary sodium excretion in Australian children.

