### The Salt and Other Nutrient Intakes in Children (SONIC) Study

The primary aim of the SONIC study was to obtain an accurate measure of total dietary sodium intake using 24-hour urinary excretion in a sample of primary schoolchildren in Victoria, Australia. Secondary aims within this sample of primary schoolchildren were: (1) to objectively measure potassium intake and the sodium to potassium ratio using 24-hour urinary electrolyte excretion, (2) to identify the dietary sources of sodium and potassium, (3) to assess the association between 24-hour urinary sodium and potassium excretion and blood pressure, (4) to assess the association between 24-hour urinary sodium excretion and body mass index (BMI) z-score and waist circumference, and (5) to identify children’s taste preferences and saltiness perception using high and low sodium variants across a range of manufactured foods, which are major dietary sources of salt.

The purpose of this paper is to describe the study design and data collection methods used within the SONIC study. In addition, we report on the recruitment outcomes and data processing procedures for determining completeness of 24-hour urine samples within the study population.

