### Anthropometry

Height, body weight, waist, and hip circumference were measured according to the protocols of the International Society for Advancement of Kinanthropometry [67]. For all measures, children were wearing light clothing with shoes removed. Height was measured to the nearest 0.1 cm using a calibrated portable stadiometer SECA (mod 220) (Hamburg, Germany). Weight was measured to the nearest 0.1 kg using a calibrated FS-127-BRW portable electronic scale (Bradman, MA, USA). A minimum of two measurements were taken for height and weight. If the two measurements were not within 5 mm for height or 0.1 kg for weight, a third measurement was taken. The mean value was used as the final score if two measurements were taken. The median value was used as the final measure if three measurements were taken. BMI was calculated as body weight (kg) divided by the square of body height (m^2^). Age and gender adjusted BMI *z*-scores will be calculated using the LMS method [68] with the 2000 US Centers for Disease Control and Prevention (CDC) Growth Charts acting as the reference population [69]. Participants will be grouped into weight categories (very underweight, underweight, healthy weight, overweight, obese) using the age and gender-specific International Obesity Task Force BMI reference cut-offs for children [70,71].

Waist and hip circumference was measured to the nearest 0.1 cm using a Lufkin Executive Thinline W606PM pocket tape (Sparks, MD, USA). Waist circumference was taken at the end of a normal expiration at the narrowest point between the lower costal border and the top of the iliac crest. Hip circumference was measured at the level of the maximum protrusion of the gluteal muscles. A minimum of two measurements were taken for waist and hip circumference. If the two measurements were not within 10 mm of the first, a third measurement was taken. The mean value was used as the final score if two measurements were taken. The median value was used as the final measure if three measurements were taken.

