### Criteria for Assessing Completeness of 24-Hour Urine Samples

If the duration of the collection was not exactly 24 hours (but within 20-28 hours), urinary sodium, potassium, creatinine, and total volume were normalized to a 24-hour period. Following this, urine collections will be considered incomplete and excluded if (1) the timing of the collection was <20 hours or >28 hours, (2) total volume was <300 mL, (3) the participant reported missing more than one collection, or (4) urinary creatinine excretion was less than 0.1 mmol/Kg body weight/day [22,41,82]. A total of 15 participants did not return their urine collection slip, so it was not possible to confirm if they had missed collections or spillages. In these children, the completeness of the 24-hour urine collection was assessed based on the other three criteria. Of the 780 participants, 757 (97.1%) had available results from the 24-hour urine collection (Figure 3). Based on the completeness criteria, 90 participants (11.5%) were classified as providing invalid 24-hour urine samples and will be excluded from analyses. Note the number of invalid urines based on the four criteria (n=125) is greater than the final number of excluded urines (n=90) as some participants’ 24-hour urine collection met more than one of the criteria for invalid urine (Figure 3).

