### Data Analysis

Descriptive statistics will be used to describe sodium and potassium intakes. Dietary sources of sodium and potassium will be determined at the individual level using the mean ratio method [84]. Liner and logistic regression models will be used to assess the association between electrolyte intake and health outcomes (blood pressure and BMI *z*-score and waist circumference) and to assess differences in taste preference and saltiness discrimination between food types, and correlations between taste preference, sodium intake, and covariates. To account for clustering of students within schools, clustered robust standard errors will be used. Analyses will be adjusted for covariates (age, gender, socioeconomic status).

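### The covariates listed for the sodium–adiposity models leave out height (for waist) and energy intake, so an aim 4 association may partly reflect larger children eating more

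*Protocol article*

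**What the plan says.** Secondary aim 4, at the end of the Introduction, is "to assess the association between 24-hour urinary sodium excretion and body mass index (BMI) z-score and waist circumference". The Data Analysis section serves it with linear and logistic regressions of the "association between electrolyte intake and health outcomes (blood pressure and BMI *z*-score and waist circumference"), using school-clustered robust standard errors. The same paragraph gives a single adjustment set for all of these models: "Analyses will be adjusted for covariates (age, gender, socioeconomic status". No other section adds height or energy intake.

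On the scale of the variables:
- **Exposure.** Sodium is an absolute daily amount. The completeness section says that "urinary sodium, potassium, creatinine, and total volume were normalized to a 24-hour period"; nothing scales it to energy or body size.
- **BMI z-score.** This is weight over height squared, standardised for age and gender.
- **Waist.** This is raw centimetres, with no ratio to height and no z-score.

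On what was collected: "Height was measured to the nearest 0.1 cm using a calibrated portable stadiometer" (Anthropometry), with no age limit stated. Energy intake comes from one dietary recall, used only from age 8, and its stated role is to flag low energy reporters (Dietary Recall).

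The Introduction's section on additional risks of sodium cites national surveys that "support the link between dietary sodium intake and obesity via greater consumption of sugar-sweetened beverages (SSBs"), and adds that "more recent evidence suggests that sodium intake is associated with adiposity, independent of energy intake".

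**The concern.** Total sodium excreted in a day depends on how much food is eaten as well as on how salty it is. Within age and gender, a bigger child may eat more and so excrete more sodium. The same child may also have a larger waist because of taller stature alone. With absolute sodium as the exposure and raw waist as the outcome, a model without height can turn body size into an apparent sodium association. BMI z-score already takes height into account, so for that outcome the gap is energy intake only.

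What is at stake is how aim 4 can be read. The background cites evidence for an association beyond energy intake, so a positive coefficient from the listed model could be taken as support for that. The model contains nothing that would separate saltier diets from larger diets.

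**Working it through.** The documents give no figure for this bias and no correlations between sodium, energy, height and adiposity. The one planning calculation, for mean sodium intake, does not bear on the point. What follows is an illustration on assumed inputs.

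**Number of children.** From the completeness section: 757 urine results − 90 invalid = 667, assuming complete covariates and outcomes.

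**Allowance for clustering.** 43 schools (Results) and ICC 0.01 (Sample Size, where it was assumed for sodium; borrowed here):
- mean cluster = 667/43 = 15.5
- design effect = 1 + (15.5 − 1) × 0.01 = 1.145
- effective n = 667/1.145 ≈ 582

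**Step 1. Spurious correlation with a true sodium effect of zero.** Given age, gender and socioeconomic status, if sodium and adiposity are linked only through energy or body size, then

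r(spurious) = r(sodium, energy/size) × r(energy/size, adiposity).

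The chance of a two-sided 5% finding uses z = atanh(r) × √(582 − 6). For example, 0.5 × 0.2 = 0.10 gives z = 0.1003 × 24.0 = 2.41, and a chance of about Φ(2.41 − 1.96) = 67%.

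| Assumed r(sodium, energy/size) | Assumed r(energy/size, adiposity) | Spurious r | Chance of significance |
|---|---|---|---|
| 0.2 | 0.1 | 0.02 | 8% |
| 0.3 | 0.2 | 0.06 | 30% |
| 0.3 | 0.3 | 0.09 | 58% |
| 0.5 | 0.2 | 0.10 | 67% |
| 0.4 | 0.3 | 0.12 | 82% |
| 0.6 | 0.4 | 0.24 | nearly 100% |

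**Step 2. What adjustment achieves for waist.** A linear simulation (400,000 records, standardised variables, no sodium effect) had height driving energy (a), energy driving sodium (b) and height driving waist (c). The expected unadjusted coefficient is a × b × c. Recalled energy was given an assumed one-day reliability of 0.4.

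| a, b, c (assumed) | a × b × c | Simulated, unadjusted | Height added | Error-free energy added | One-day energy added |
|---|---|---|---|---|---|
| 0.3, 0.4, 0.3 | 0.036 | 0.035 | about 0 | about 0 | 0.022 |
| 0.3, 0.5, 0.5 | 0.075 | 0.075 | about 0 | about 0 | 0.050 |
| 0.4, 0.5, 0.5 | 0.100 | 0.100 | about 0 | about 0 | 0.065 |
| 0.5, 0.6, 0.6 | 0.180 | 0.182 | about 0 | about 0 | 0.129 |

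Height removes the bias completely here because the simulation makes height the only common source; real data would be less tidy. One-day energy leaves 0.022/0.035 = 63% to 0.129/0.182 = 71% of the bias. Energy adjustment from a single recall is therefore informative but far from complete.

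**The case against.** **The aim is only an association.** The stated gap is the lack of Australian work using 24-hour urinary sodium, and aim 4 asks for an association. A reader might infer that the listed model cannot answer the question the Introduction poses. The documents do not support that: the model estimates the association named, and no energy-independent estimate is promised. What stands is a limit on interpretation.

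**Beverages are a pathway.** The cited surveys place sugar-sweetened beverages between sodium and obesity. Adjusting for them, or for the energy they carry, may remove part of the effect of interest. This is right, and leaving beverages out of the main model is defensible.

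**Recall energy is a weak adjuster.** It covers one day, is used only from age 8, and runs midnight to midnight on the day before interview, while urine could be collected over a school day or any 24 hours of a weekend. The article itself acknowledges the age limit and the single day. This is a fair reason to keep energy out of the main model. It is no reason to omit a secondary one, and it does not touch height.

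**Age and gender already absorb much of height.** They take out part of it; the concern is the variation left within age and gender.

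**This is a condensed article.** Outcome-specific models may sit in a fuller plan that is not shown. But the article states a covariate list rather than leaving it open, and the list as stated does not suit a raw waist outcome.

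**Conclusion.** The point holds in a limited form. The stated adjustment set omits height from the waist model and energy intake from both adiposity models, so an aim 4 association may partly reflect larger children eating more within age and gender. The size cannot be derived from the documents. With assumed correlations of 0.2 to 0.6 (sodium with energy or size) and 0.1 to 0.4 (energy or size with adiposity), the spurious partial correlation is 0.02 to 0.24, and the chance of a significant result with no sodium effect is about 8% to nearly 100%.

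It is tempting to say that a positive slope is almost guaranteed. The low end of that range shows why this cannot be claimed. Nor would an energy-adjusted model settle independence from energy, since at the assumed reliability roughly two thirds of the bias remains. The matter concerns one of five secondary aims and leaves the primary aim, measuring sodium intake, untouched. It should still be put right, because it changes what aim 4 can conclude at little cost.

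**What to change.** 1. **Waist model.** In all children with valid urines, add height to the listed covariates, or use waist-to-height ratio as the outcome.
2. **Main result.** Keep the listed covariates (with the height change for waist) as the main model, and report it as the total association. Do not describe it as independent of energy intake.
3. **Secondary energy model.** In children aged 8 and over whose recall is not classed as low energy reporting, fit the model with energy intake and, beside it, the same model without energy in the same subset. The pairing separates the effect of adjustment from that of dropping younger children.
4. **Beverages.** If a model with sugar-sweetened beverages is added, label it an exploration of a mediator, not control of a confounder.
5. **Wording.** State that the energy-adjusted result is only partly adjusted, because it rests on one recall day that may not match the urine day.

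The cost is two or three extra models on data already collected; the article says analysis was still under way. The height change loses no children by design. The energy model is confined to a smaller subset, whose size the article does not give, and will be less precise.

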## Results

Data collection was completed in May 2013. A total of 780 children across 43 schools participated. Data analysis is currently underway and results are expected at the end of 2015.

## Discussion

### Strengths and Limitations

This study will provide the first objective measure of sodium and potassium intakes in Australian schoolchildren. The major strength of this study is the use of 24-hour urine collections to assess total daily sodium intake in a large sample of schoolchildren. Furthermore, a well-devised 24-hour urine collection protocol, tailored specifically to children was used. Limitations of the study include the convenience sampling framework and the low response rate, which limits the generalizability of the study findings. In addition, dietary recall data is only available on those children aged 8 years and above and only 1 day of recall data was collected.

### Conclusion

Given the cardiovascular implications of consuming too much sodium and too little potassium, monitoring of these nutrients during childhood is an important public health initiative. The methods described within provide a platform for other research groups and public health organizations to conduct 24-hour urinary sodium and potassium measurements in wide-ranging children and potentially adolescent populations, thus adding to the evidence base exploring the intake of these important electrolytes, their implications of health in the early stages of life, and the potential impact on food choice.

## Abbreviations

AI: adequate intake
BMI: body mass index
CNPAS: Children’s Nutrition and Physical Activity Survey
CVD: cardiovascular disease
EI: estBMR: energy intake:estimated basal metabolic rate
estBMR: estimated basal metabolic rate
ICC: intra-cluster correlation
SONIC: Salt and Other Nutrient Intakes in Children study
SSB: sugar-sweetened beverage
